# Protocol Treatment

- 1. Treatment Schedule

Use actual weight or estimated dry weight if fluid retention Cycle 1 treatment = 28 days

All subsequent treatment cycles = 21 days (±3 days)

| Drug | Dose | Treatment | Retreatment |
| --- | --- | --- | --- |
| Ibrutinib | assigned at registration | PO daily (Day 1 to 28  of Cycle 1, then Day 1- 21* on subsequent cycles) | Every 21 days  (±3 days)  until confirmed progression |
| Pembrolizumab | 200 mg | IV injection on Day 8 of Cycle 1 and then Day 1 of each  subsequent cycle | Every 21 days (±3 days) until confirmed progression |

* Patients should receive a sufficient quantity of ibrutinib to last until the next scheduled treatment visit.

- 1. Determination of Maximum Tolerated Dose (MTD)
  2. Dose Escalation Scheme

| Dose level | Ibrutinib** |
| --- | --- |
| -1 | 140 mg |
| 0* | 280 mg |
| 1 | 420 mg |

* Starting dose level

** If the patient has clinical or laboratory evidence of liver failure during the treatment, then calculate the Child-Pugh score and adjust the ibrutinib dose (see Table 8.3).

NOTE: Doses will not be escalated in any individual patient.

- 1. MTD Determined

As of MCCC Amendment 6, the MTD has been determined to be Dose Level 1. Dose Level 1 will be used for the expansion cohort.

- 1. Dose Limiting Toxicities

Dose limiting toxicities (DLT) are defined to be:

| ***Toxicity*** | ***DLT Definition*** |
| --- | --- |
| Hematologic | Grade 4 ANC, Grade 4 Hgb, or PLT <25,000 |
| Renal | Serum creatinine ≥2 times baseline |
| Neurologic | ≥Grade 2 neurosensory or neuromotor toxicity |
| Other nonhematologic | ≥Grade 3 per NCI Common Terminology Criteria for Adverse Events (CTCAE) version 4.0* |

*Grade 3 rash or fever despite maximal supportive treatment(s) will be considered dose-limiting; all grade 4 rash and fever will be considered a DLT.

The maximum tolerated dose is defined as the highest dose level among those tested where at most one out of 6 patients develops a DLT prior to the start of their second cycle of treatment and the next highest dose level is such that 2 out of a maximum of 6 patients treated at this dose level developed a DLT prior to the start of their second cycle of treatment.

- 1. Dose escalation plan

NOTE: As of MCCC Amendment 6, the MTD has been determined to be Dose Level 1. A minimum of 2 or a maximum of 6 patients will be accrued to a given dose level.

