|  | Grade 4 | Discontinue and enter Event Monitoring  Initiate systemic steroid treatment (see Section 9.6) | Discontinue and enter Event Monitoring |
|  | **Nausea and Vomiting** | | |
|  | Grade ≥3 despite optimal  anti-emetic therapy | Continue if Grade 3  Hold if >Grade 3 until resolves  to ≤Grade 1 | Hold  Resume according to Table 8.2 |
| Investigations | Hepatic Dysfunction (**AST** or **ALT** or total **bilirubin**) and immune-mediated hepatitis | | |
|  | Grade 2  (AST or ALT >3 × and  <5 × ULN  or total bilirubin >1.5 × and <3 × ULN) | *Hold until levels resolve to  ≤Grade 1  (AST or ALT ≤3× ULN,  total bilirubin ≤1.5 × ULN)  Consider initiating systemic steroid treatment (see Section 9.6)  Discontinue if does not resolve to ≤Grade 1 within 12 weeks after last dose administration,  and enter Event Monitoring | Hold until pembrolizumab resumed  Resume at the next lower dose level (if occurs at 140 mg once daily, discontinue).  Discontinue if pembrolizumab is discontinued, and enter Event Monitoring |
|  | Grade 3  (AST or ALT >5 × ULN or  total bilirubin >3 ×ULN) or for patients with liver metastasis who begin treatment with Grade 2 AST or ALT, if AST or ALT increases by greater than or equal to 50%  relative to baseline and lasts ≥1 week | Discontinue and enter Event Monitoring  Initiate systemic steroid treatment (see Section 9.6) | Discontinue and enter Event Monitoring. |
| Immune System Disorders | **Immune-related Adverse Events** | | |
|  | Grade 2 | *Hold until symptoms resolved to ≤Grade 1, initiate systemic steroid (see 9.6). Discontinue if does not resolve to ≤Grade 1 within 12 weeks after last dose administration, and enter Event Monitoring. | Hold until pembrolizumab resumed. Resume at the next lower dose level (if occurs at 140 mg once daily, discontinue).  Discontinue if pembrolizumab is discontinued, and enter Event Monitoring |
|  | Grade ≥3 (except gastrointestinal and endocrine disorders) | Discontinue and enter Event Monitoring  Initiate systemic steroid treatment | Discontinue and enter Event Monitoring |

| **System/Organ/Class (SOC)** | **ADVERSE EVENTS/SYMPTOMS** | **ACTIONS** | |
| --- | --- | --- | --- |
|  |  | **Pembrolizumab** | **Ibrutinib** |
| Infections and | **Infectious Disorders** | | |
| infestations | Grade ≥3 | *Hold  If ibrutinib is held resume if  ≤Grade 1 or baseline | Hold until ≤Grade 1 or  baseline  Resume at the next lower dose level (if occurs at 140 mg once  daily, discontinue). |

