|  | Grade 2 | *Hold pembrolizumab until resolves to ≤Grade 1 Discontinue if does not resolve to ≤Grade 1 within 12 weeks after last dose administration | Hold until pembrolizumab is resumed  Resume at the next lower dose level (if occurs at 140 mg once daily, discontinue).  Discontinue if pembrolizumab  is discontinued, and enter Event Monitoring |

| **System/Organ/Class (SOC)** | **ADVERSE EVENTS/SYMPTOMS** | **ACTIONS** | |
| --- | --- | --- | --- |
|  |  | **Pembrolizumab** | **Ibrutinib** |
|  | Grade ≥3 | Hold pembrolizumab. If resolves to ≤Grade 1 within 72 hours resume treatment  If not, discontinue and enter Event Monitoring | Hold until pembrolizumab resumed  Resume at the next lower dose level (if occurs at 140 mg once daily, discontinue).  Discontinue if pembrolizumab is discontinued, and enter Event Monitoring |
| Other non-laboratory Adverse Events |  | | |
|  | Grade 3 | *Hold pembrolizumab until resolves to ≤Grade 1 Discontinue if does not resolve to ≤Grade 1 within 12 weeks after last dose administration | Hold until pembrolizumab resumed Resume at the next lower dose level (if occurs at 140 mg once daily, discontinue).  Discontinue if pembrolizumab is discontinued, and enter Event Monitoring |
|  | Grade 4 | Discontinue and enter Event Monitoring | Discontinue and enter Event Monitoring |

*If ibrutinib is discontinued according to Table 8.2, continue pembrolizumab until disease progression or intolerance develops or patient refusal.

- 1. Modifications Based on Concomitant Medications and Procedures for Ibrutinib
     - **Dose Modifications for Use with CYP3A Inhibitors and Inducers**

Ibrutinib is metabolized primarily by CYP3A. Avoid co-administration with strong CYP3A4 or moderate CYP3A inhibitors and consider alternative agents with less CYP3A inhibition.

- - - - If a strong CYP3A inhibitor (eg, ketoconazole, posaconazole, indinavir, nelfinavir, ritonavir, saquinavir, clarithromycin, telithromycin, itraconazole, nefazadone, or cobicistat) must be used, reduce ibrutinib to 140 mg for the duration of the inhibitor or withhold ibrutinib treatment temporarilty (for 7 days or less). Pembrolizumab may be continued at current dose. If unable to discontinue strong CYP3A inhibitor use within 12 weeks then permanently discontinue ibrutinib.

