# Statistical Considerations and Methodology

- 1. Background

A 3+3 phase I clinical trial design will be used to determine the maximum tolerated dose of Ibrutinib when used in combination with Pembrolizumab in patients with metastatic melanoma who are Ipilimumab-naïve in the metastatic setting. Once determined, a dose expansion cohort will be used to determine an early signal of promising anti-tumor activity measured by tumor response.

- 1. Study Design – Phase I
  2. Definition of Maximum Tolerated Dose (MTD)

The maximum tolerated dose is defined as the highest dose level among those tested where at most one out of 6 patients develops a DLT prior to the start of their second cycle of treatment and the next highest dose level is such that 2 out of a maximum of 6 patients treated at this dose level developed a DLT prior to the start of their second cycle of treatment.

- 1. Enrollment and determination of MTD

16.221 A minimum of 2 or a maximum of 6 patients will be accrued to a given dose level.

For each dose level, patients will be accrued so that at any given time no more than 2 patients will be receiving their first cycle of treatment **and** acute adverse event data over the first treatment cycle for all other patients treated at the current dose level is known.

16.222 If, at any time in the enrollment process, 2 patients treated at the current dose level develop a DLT during the first cycle of treatment, enrollment will be closed to that dose level. Enrollment will be re-opened to the next lower dose level if fewer than 6 patients have been treated at that dose level in order to establish whether it is the MTD.

If none of the first 3 patients treated at a given dose level develops a DLT during the first cycle of treatment, enrollment to the dose level will be closed and enrollment will reopen at next higher dose level. If there are no other higher dose levels to be tested, three additional patients will enrolled at the current dose level to confirm MTD.

If one of the first 3 patients treated at a given dose level develops a DLT during the first cycle of treatment, three additional patients will enrolled (sequentially) onto the current dose level.

- If, at any time in the enrollment of these 3 additional patients, a patient develops a DLT, enrollment will be closed to this dose level. Enrollment will be re-opened to the next lower dose level if fewer than 6 patients have been treated at that dose level.

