- If none of these 3 additional patients develops a DLT during the first cycle of treatment, enrollment to this dose level will be closed and enrollment will reopen at next higher dose level. If there are no other higher dose levels to be tested, this will be considered the MTD
  1. Study Design – Expansion Cohort (Treated at MTD)

Acknowledging both the short term aspect of the primary endpoint of the study and that 18 patients may be enrolled, we have chosen a phase II study design proposed by Gehan30. Two (2) responses in 14 eligible patients having initiate treatment will be considered indicative of promising activity and further study in a phase 2 study. According to Gehan, if a drug were 20 percent effective or more, there would be a 95% chance that one or more successes would be obtained in 14 patients^30^.

Gehan’s approach calculated cumulative probability of observing at most x successes in N patients (i.e., assuming a binomial distribution) assuming the true success rate is P.

Assuming true success (response) proportion in 14 patients is P=20%:

| If the number of responses (x) observed… | Then the probability of observing  ≤ x responses is less than or equal  to… |
| --- | --- |
| 0 | 0.044 |
| 1 | 0.198 |
| 2 | 0.448 |
| 3 | 0.698 |

Assuming true success (response) proportion in 14 patients is P=30%:

| If the number of responses observed… | Then the probability of observing  ≤ x responses is less than or equal  to… |
| --- | --- |
| 0 | 0.007 |
| 1 | 0.047 |
| 2 | 0.161 |
| 3 | 0.355 |

Two planned safety checks will occur after 3 and 6 patients have completed their first cycle of treatment. If we observe DLT(s) at either review of the data (1 DLT in the first 3 patients or 2 DLTs in the first 6 patients), we will drop the starting dose level to 280 mg and continue with the remainder of the study. Only one reduction in the starting dose level will be allowed. All data will be summarized by assigned starting dose level and by prior ICI therapy status.

- 1. Sample Size

Enrollment and anticipated number of patients, phase of study:

- - - Prior to MCCC Amendment #2, two patients were enrolled and the study was stopped due to toxicity. The study reopened was modified to a phase I (vs phase II).
    - Phase I - During the dose escalation phase, a minimum of 9 and a maximum of 18 patients is anticipated. Enrollment was completed prior to MCCC Amendment #6 (11 patients).

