    - Phase I Dose Expansion: At the time of MCCC Amendment #6, 6 patients were enrolled at the MTD (Dose Level 1). Fourteen (14) patients are required for the dose expansion cohort component of this study. Assuming that these 6 patients

are included in the expansion cohort, an additional 8 patients are required for the design. Accounting for 2 non-evaluable patients (e.g, ineligible, cancellations), an additional 10 (i.e., 8 + 2) patients will be enrolled at the MTD to gain additional insight into the safety profile and clinical benefit of this treatment strategy (i.e., dose expansion cohort). That is, maximum enrollment is 16 patients.

Final enrollment is expected to be 2 (original phase II design) plus 5 treated at Dose Level 0 (phase I design), plus 16 [6 treated at dose level 2 of phase I design, plus the expansion cohort mentioned above (10)]. That is, final enrollment for the entire study is expected to be a maximum of 23 patients.

- 1. Accrual Duration:

We anticipate that approximately 10% of the patients who pre-register will fail to meet the criteria for registration or met the criteria for registration but refuse to continue.

2 patients will be enrolled per month during the dose expansion.

Given the nature of the accrual scheme, it will take 11-24 months to complete enrollment to the dose escalation phase (2 pts per month and a 1 month gap between each set of 2 pts) and then an additional 5-6 months to enroll the dose expansion cohort and associated with MCCC Amendment 6.

- 1. Definition of end points and analysis plan:

Patient evaluability: All patients meeting the eligibility criteria who have signed a consent form and have begun treatment will be included in the analysis of the safety and clinical outcome data.

The primary endpoints:

- - - Phase I/Dose Seeking: The endpoint is the maximum tolerated dose (MTD). The maximum tolerated dose (MTD) is defined as the highest dose level among those under consideration where at most 1 of 6 patients develops a dose limiting toxicity and 2 or more of the 3-6 patients treated at the next higher dose level develop a dose limiting toxicity.

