16.71 Safety Stopping rules

Dose limiting toxicities and other acute adverse events will be monitored by the study team on a monthly basis. If during the course of enrolling the first 6 patients on trial, 2 patients develop a grade 3+ maculo-papular rash, pneumonitis, nephritis, fever, allergic reaction, anaphylaxis, dyspnea, or increased blood bilirubin or grade 4 hyperthyroidism, hypophysitis or diarrhea, which are considered possibly, probably, or definitely related to treatment, any time during treatment enrollment will be temporarily closed.

Any time after the first 6 patients have been enrolled, if 30% or more of the patient enrolled develop one (or more) of the toxicities listed in the table below during treatment or within 30 days of discontinuing protocol treatment and the toxicity is considered to be possibly, probably, or definitely related to treatment, enrollment will be temporarily closed.

| **Toxicity** | **Severity/duration** |
| --- | --- |
| Neurologic | Grade 2 and not resolved to ≤ Grade 1 within 14 days  ≥ Grade 3 regardless of time to resolution |
| Hematologic | Grade 4 and not resolved to ≤ Grade 1 within 14 days  Grade 3 with Grade 3+ febrile neutropenia or hemorrhage, regardless of time to resolution |
| Other | Grade 3 and not resolved to ≤ Grade 1 within 14 days  Grade 4 regardless of time to resolution  Any toxicity that leads to treatment discontinuation due to toxicity |

- 1. Inclusion of Women and Minorities

| **Accrual Targets** | | | |
| --- | --- | --- | --- |
| **Ethnic Category** | **Sex/Gender** | | |
|  | **Females** | **Males** | **Total** |
| Hispanic or Latino | 0 | 1 | 1 |
| Not Hispanic or Latino | 10 | 12 | 22 |
| **Ethnic Category: Total of all subjects*** | **10** | **13** | **23** |
| **Racial Category** | | | |
| American Indian or Alaskan Native |  |  |  |
| Asian |  |  |  |
| Black or African American |  |  |  |
| Native Hawaiian or other Pacific Islander |  |  |  |
| White | 10 | 13 | 23 |
| **Racial Category: Total of all subjects*** | **10** | **13** | **23** |

| **Ethnic Categories:** | **Hispanic or Latino –** a person of Cuban, Mexican, Puerto Rican, South or Central American, or other Spanish culture or origin, regardless of race. The term “Spanish origin” can also be used in addition to “Hispanic or Latino.”  **Not Hispanic or Latino** |
| --- | --- |

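### Section 16.3 lowers the expansion dose only at scheduled reviews, so patients can still start ibrutinib at 420 mg after the DLT threshold for 280 mg has been met

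*Protocol*

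**What the plan says.** Section 16.3 sets two looks at the expansion cohort: "Two planned safety checks will occur after 3 and 6 patients have completed their first cycle of treatment". The action is tied to those looks: "If we observe DLT(s) at either review of the data", with 1 DLT in the first 3 patients or 2 in the first 6, the starting dose becomes 280 mg and the study continues. Only one such reduction is allowed.

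The expansion begins at Dose Level 1, 420 mg, because "As of MCCC Amendment 6, the MTD has been determined to be Dose Level 1" (Section 7). Section 16, Accrual Duration, states: "2 patients will be enrolled per month during the dose expansion". Cycle 1 lasts 28 days (Section 4).

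Section 16.71 adds monthly DLT monitoring by the study team and a temporary closure of enrollment: "Any time after the first 6 patients have been enrolled, if 30% or more of the patient enrolled develop" one of a separate list of toxicities. Section 16 also has reports going to the DSMB every 3 months.

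**The concern.** Both thresholds are irreversible. If one of the first three patients has had a DLT, nothing that later patients do can bring the count back to zero. The sponsor has already decided that this result calls for 280 mg. Section 16.3 nevertheless requires no action until the third (or sixth) patient has finished Cycle 1 and sets no pause in enrollment. A patient can therefore be started at 420 mg when the protocol's own criterion for 280 mg is satisfied, and that patient's outcome cannot change the decision.

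A second, smaller point concerns who counts as having completed Cycle 1. Table 8.2 ends both drugs for several DLT-grade events. Examples are immune-related events of "Grade ≥3 (except gastrointestinal and endocrine disorders"), Grade 3 hepatic events, and Grade 3 or higher pneumonitis, kidney injury or infusion reaction. Grade 3 or higher rash leads to the same end unless it settles quickly ("Hold pembrolizumab. If resolves to ≤Grade 1 within 72 hours resume treatment"). Section 16.3 does not say whether such a patient advances the count to 3 or 6. If not, a toxicity stop would postpone the toxicity review.

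**Working it through.** **Inputs from the protocol.** 10 new patients at 2 per month (Section 16, Sample Size and Accrual Duration): 10 / 2 = 5 months, which agrees with the stated 5 to 6. Cycle 1 is 28 days, with pembrolizumab first given on Day 8 (Section 7).

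**Assumptions, not in the documents.** DLT rate p from 5% to 30% (Section 7 allows at most 1 in 6 observed at the MTD). DLT onset uniform over Days 8 to 28. Starts every 15.2 days (even) or in pairs every 30.4 days. Review held on the day the count is reached. The checks count the 10 new patients, since the six carried over were already assessed in escalation.

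**1. Chance that the check 1 threshold is met.** 1 − (1 − p)³ = 0.14 (p = 5%), 0.27 (10%), 0.42 (1/6), 0.66 (30%).

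**2. Even accrual, DLT patients counted at Day 28.**
- Starts fall on days 0, 15.2, 30.4 and 45.6. The third patient finishes Cycle 1 on day 30.4 + 28 = 58.4, and patient 5 would start on day 60.8. Only patient 4 lies beyond the first three.
- A DLT precedes the next start with probability (15.2 − 8)/20 = 0.36 and always precedes the start after that (28 < 30.4).
- Starts after the threshold and before the check: 2.36 if patient 1 has a DLT; 1.36 if patient 2 is the first in order with one; 0.36 if only patient 3 has one.
- Mean, given that the threshold is met: [2.36p + 1.36(1 − p)p + 0.36(1 − p)²p] / [1 − (1 − p)³] = 1.39 (5%), 1.48 (1/6), 1.59 (30%).
- Patient 4 alone: [p + (1 − p)p + 0.36(1 − p)²p] / [1 − (1 − p)³] = 0.80 (5%), 0.86 (30%).
- If a stopped patient counts from the day of stopping, the check comes slightly earlier. Simulation (200,000 runs per cell, 25% to 100% of DLT patients stopping) gives 1.3 to 1.5 in total, with 0.7 to 0.8 beyond the first three.

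**3. Paired accrual.** Patients 3 and 4 start on day 30.4 and the check falls on day 58.4. A DLT in patient 1 or 2 always leaves two later starts; a DLT only in patient 3 leaves none. Mean: 2[1 − (1 − p)²] / [1 − (1 − p)³] = 1.37 (5%) to 1.55 (30%), half of it patient 4.

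Over steps 2 and 3, with stoppers counted on stopping, the range is about 1.3 to 1.6.

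**4. Assumed 7-day lag to confirm a DLT, even accrual.** Confirmation then falls on Days 15 to 35. It precedes the next start with probability (15.2 − 15)/20 = 0.01 and the one after with (30.4 − 15)/20 = 0.77. The three values become 1.78, 0.78 and 0.01, and the mean is 0.89 (5%), 0.96 (1/6) and 1.06 (30%): about one patient.

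**5. Literal reading of completion (stoppers not counted).** With even accrual, one stop among the first three moves the check to 45.6 + 28 = day 73.6, with 5 started instead of 4. With paired accrual one stop adds no delay; two stops in the first pair move the check to 60.8 + 28 = day 88.8. Simulated means, given that the threshold is met: 1.7 to 3.5 (even) and 1.4 to 2.9 (paired). The upper ends need a 30% DLT rate and every DLT patient stopping.

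**6. Check 2.** It decides the dose only after a DLT-free first three and then at least 2 DLTs in the next three: (1 − p)³ × P(Bin(3, p) ≥ 2) = 0.006 (5%), 0.043 (1/6), 0.074 (30%). It rarely matters.

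**7. Backstops.** Section 16.71 attaches no dose action to monthly monitoring. The 30% rule, read over all enrolled, already carries 2 + 11 = 13 patients. At 14 enrolled it needs 0.30 × 14 = 4.2, so 5 affected patients, and it closes enrollment temporarily without lowering the dose.

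**The case against.** The strongest reply is that this is a legitimate design choice. Section 16.3 has two scheduled looks, stated thresholds and a stated action, and nothing in it is contradictory. The later starters receive the declared MTD. About half of the further patients are numbers 2 and 3 of the cohort the sponsor chose to review as a unit. A DLT also takes time to establish: Grade 3 rash or fever counts only if it persists despite maximal supportive care (Section 7). These points stand. They limit the size of the concern but do not explain why a threshold that cannot be reversed should wait for a date.

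Three stronger readings are tempting and not supported.
- A reader might infer that the escalation rule sets a precedent for acting at once on 1 DLT in 3. It does not. In 16.222 the any-time closure needs two DLTs; after one in three, "three additional patients will enrolled (sequentially) onto the current dose level".
- A reader might infer that DLTs in patients who stop early are lost. They are not, because the action clause counts the first 3 and first 6 patients, not completers.
- A reader might take 3.5 extra patients as the expected effect. That needs the literal reading of completion. The replacement rule in Section 7 replaces only patients who miss Cycle 1 for reasons other than toxicity, which suggests that toxicity stoppers stay evaluable. Some DLTs, such as Grade 3 diarrhea or Grade 4 neutropenia, only hold treatment.

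**Conclusion.** The timing gap holds. Section 16.3 allows new patients to start at 420 mg after the sponsor's own irreversible criterion for 280 mg is met, and no other rule lowers the starting dose. On the stated assumptions the effect is modest: when the check 1 threshold is met, between one and two of the 10 new patients. The exact figure depends on the DLT rate, on onset timing and on how quickly a DLT is confirmed, none of which the protocol fixes. Who counts as having completed Cycle 1 is a wording clarification, not a second defect of equal weight. Nothing here shows that 420 mg is unsafe or that the thresholds are wrong. Severity is minor to moderate.

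**What to change.** Add to Section 16.3:
- New patients start at 280 mg as soon as a confirmed DLT brings the count to 1 in the first 3 or 2 in the first 6, without waiting for the scheduled review.
- A patient counts towards the 3 and the 6 on completing Cycle 1, on having a DLT, or on stopping for toxicity in Cycle 1.

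The thresholds, the dose step and the limit of one reduction stay as they are. If the sponsor prefers to act only at the reviews, the second sentence alone removes the ambiguity about the trigger.

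The change needs no extra patients or procedures. Its price is that, when the threshold is met, about one to two fewer of the 10 new patients contribute response data at 420 mg, the dose at which the expansion is meant to estimate response.

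### After the one permitted drop to 280 mg, Section 16.3 ties no action to any DLT count among patients started at that dose: a modest gap that is cheap to close

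*Protocol*

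**What the plan says.** Section 16.3 of the Protocol (expansion cohort, treated at the MTD) plans checks after 3 and after 6 patients have completed Cycle 1. The trigger is "1 DLT in the first 3 patients or 2 DLTs in the first 6 patients". The response is the same at both: "we will drop the starting dose level to 280 mg and continue with the remainder of the study". The paragraph then adds "Only one reduction in the starting dose level will be allowed".

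Other text bears on what happens after a reduction:

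- **Phase I rule (Sections 7 and 16.222).** Two DLTs close a dose level. The rule is written for the escalation, which finished before Amendment 6. There, the clause beginning "If one of the first 3 patients treated at a given dose level develops a DLT during the first cycle of treatment" leads only to three more patients at the same level.
- **Section 16.71.** "Dose limiting toxicities and other acute adverse events will be monitored by the study team on a monthly basis". No count is attached to that review. After the first 6 patients, enrollment closes temporarily "if 30% or more of the patient enrolled develop one (or more) of the toxicities listed in the table below", provided the toxicity is at least possibly related.
- **Section 16, Monitoring of the trial.** The DSMB receives an accrual and adverse event report every 3 months.
- **Section 16.4.** Ten new patients are planned at the MTD, 5 patients were treated at 280 mg in phase I, and total enrollment is at most 23.

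**The concern.** The checks have one action and it can be used once. If the first check triggers it, the check at 6 is still scheduled but has nothing left to do. If the second check triggers it, no check remains. Either way, patients then start at 280 mg with no dose-specific DLT limit, and the written instruction is to continue.

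If two or more of these 4 to 7 patients had a first-cycle DLT, a pause would depend either on unscripted judgment at the monthly review or on the 30% rule. That rule is not split by dose and uses a toxicity list different from the DLT definition. In the escalation, two DLTs at a level closed it. Section 16.3 returns patients to the same 280 mg level without carrying that limit over.

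**Working it through.** **The plan's own figures.** Section 16.3 gives no operating figure for its safety checks. Its only probabilities are the response tables for 14 patients, and these reproduce: P(X ≤ 0, 1, 2, 3) = 0.0440, 0.1979, 0.4481, 0.6982 at 20%, and 0.0068, 0.0475, 0.1608, 0.3552 at 30%.

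**Inputs.** Triggers are 1 of 3 or 2 of 6 (Section 16.3), with 10 new patients (Section 16.4). Assumptions, because the Protocol gives no DLT rates:

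- the checks count new patients;
- the Cycle 1 DLT rate at 420 mg is p = 10%, 1/6 or 25%;
- the rate at 280 mg is q = p or q = p/2.

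**Patients exposed.** At most 10 − 3 = 7 after a first-check drop and 10 − 6 = 4 after a second-check drop. At 2 patients per month without a pause, patient 3 completes Cycle 1 on about day 58 with 4 enrolled, and patient 6 on about day 104 with 7 enrolled. This leaves 6 and 3.

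**Chance of a reduction.** First check: 1 − (1 − p)³. Second check only: (1 − p)³ × P(Bin(3, p) ≥ 2).

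| p | First check | Second check only | Either |
|---|---|---|---|
| 10% | 0.271 | 0.020 | 0.291 |
| 1/6 | 0.421 | 0.043 | 0.464 |
| 25% | 0.578 | 0.066 | 0.644 |

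**Reduction, then 2 or more DLTs at 280 mg.** P(first) × P(Bin(n₁, q) ≥ 2) + P(second only) × P(Bin(n₂, q) ≥ 2).

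| p | q = p; 7 and 4 | q = p/2; 7 and 4 | q = p; 6 and 3 | q = p/2; 6 and 3 |
|---|---|---|---|---|
| 10% | 0.042 | 0.012 | 0.032 | 0.009 |
| 1/6 | 0.145 (0.1448) | 0.048 | 0.114 | 0.036 |
| 25% | 0.338 | 0.129 | 0.280 | 0.099 |

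Example, p = q = 25%: 0.578 × 0.555 + 0.066 × 0.262 = 0.338. None of these figures removes trials that Section 16.71 would have closed.

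**What Section 16.71 catches.** It counts at once any related toxicity that ends treatment. Section 8, to be followed strictly in Cycle 1, requires discontinuation of both drugs for related Grade 3 or higher hepatic toxicity, pneumonitis, kidney injury and most immune-related events, and for Grade 3 or higher rash not down to Grade 1 within 72 hours.

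**What it omits.** DLTs that resolve within 14 days without ending treatment. For example, the hematologic DLT definition is "Grade 4 ANC, Grade 4 Hgb, or PLT <25,000" with no duration, whereas 16.71 asks for "Grade 4 and not resolved to ≤ Grade 1 within 14 days" (or Grade 3 with febrile neutropenia or hemorrhage). Short-lived Grade 3 diarrhea and Grade 2 neurologic toxicity also fall outside it.

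**How soon it acts.** Read over the whole trial, enrollment is 2 + 5 + 6 + 3 = 16 when the third new patient enters, so 0.3 × 16 = 4.8 means 5 affected. At 23 patients, 6.9 means 7. With 7 patients at 280 mg and a 40% rate of listed events among them, closure has probability 0.10 if 2 earlier patients had qualifying events and 0.66 if 4 had (assumed counts). Read over the 10 new patients only, with 1 earlier event, it is 0.84.

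**The case against.** The strongest reply is that the trial is not left without protection, and much of it stands. The dose after reduction is below the declared MTD, was given to 5 patients, and is the level from which escalation moved up. DLTs are reviewed monthly. Section 16.71 captures most of the serious toxicity that matters, including persistent rash, the event that led the original study to be redesigned. What escapes is mainly reversible toxicity, and Section 8 already holds and reduces dosing for many such events. A reader might infer that Section 16.3 leaves patients at 280 mg with no stopping rule. The documents do not support that: what is missing is a DLT limit specific to the 280 mg starting dose.

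A reader might also take a reduction as evidence that 420 mg is intolerable. One DLT in 3 patients is enough to trigger it, and in phase I the same result only added patients at that level.

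Two points about the numbers stand as well. The higher figures need a 25% DLT rate at a dose that phase I declared the MTD, plus equal toxicity at 280 mg. And if the 30% rule were counted over the new expansion patients alone, it would do almost all the work of a new rule. Its wording leaves the denominator open, but its companion clause on the first 6 patients on trial favors the whole-trial reading, under which it is slower.

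The objection does not remove the point. No surviving provision attaches a step to DLTs at 280 mg, and the 30% rule mixes dose levels. With expansion accrual planned over 5 to 6 months, quarterly DSMB reports may come late.

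**Conclusion.** The point holds as a modest gap. After the single drop, Section 16.3 links no DLT count among the at most 7 or 4 patients started at 280 mg to any action, and its instruction is to continue.

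A reduction is a realistic path: 29%, 46% or 64% of trials at assumed 420 mg DLT rates of 10%, 1/6 or 25%. A reduction followed by 2 or more DLTs at 280 mg occurs in 1% to 4%, 5% to 14% and 13% to 34% respectively, the range running from half to equal toxicity at the lower dose, with the maximum 7 and 4 patients. These figures should not be read as the chance that unsafe enrollment would continue. They are upper bounds on the gap, because Section 16.71 would close some of these trials and the documents do not allow that share to be fixed. All of them rest on assumed DLT rates and on the checks counting new patients, which Section 16.3 does not state.

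**What to change.** Add to Section 16.3:

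> If the starting dose is lowered to 280 mg, the DLT count restarts at zero for patients assigned to 280 mg, and 2 Cycle 1 DLTs among them suspend enrollment pending MCCC DSMB review. The checks at 3 and 6 count newly enrolled expansion patients.

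The second sentence is needed because Section 16.4 places the 6 phase I patients in the same cohort.

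The chance that the new rule pauses accrual is P(Bin(n, r) ≥ 2):

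| True DLT rate r at 280 mg | n = 7 | n = 4 |
|---|---|---|
| 5% | 4% | 1% |
| 10% | 15% | 5% |
| 25% | 56% | 26% |
| 40% | 84% | 52% |

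The benefit is clear after a first-check drop and limited after a second-check drop. The change takes two sentences by amendment and uses the existing study team and DSMB. Its downside is a possible short accrual pause, which is uncommon when the true rate is low.
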